# Does the use of the Informed Healthcare Choices (IHC) primary school resources improve the ability of grade-5 children in Uganda to assess the trustworthiness of claims about the effects of treatments: protocol for a cluster-randomised trial

**DOI:** 10.1186/s13063-017-1958-8

**Published:** 2017-05-18

**Keywords:** Critical thinking, Critical appraisal, Higher-order thinking, Meta-cognition, Treatment claims, Health literacy, Evidence-based health care, EBM teaching resources, Primary school curriculum, Science teaching

## Abstract

**Background:**

The ability to appraise claims about the benefits and harms of treatments is crucial for informed health care decision-making. This research aims to enable children in East African primary schools (the clusters) to acquire and retain skills that can help them make informed health care choices by improving their ability to obtain, process and understand health information. The trial will evaluate (at the individual participant level) whether specially designed learning resources can teach children some of the key concepts relevant to appraising claims about the benefits and harms of health care interventions (treatments).

**Methods:**

This is a two-arm, cluster-randomised trial with stratified random allocation. We will recruit 120 primary schools (the clusters) between April and May 2016 in the central region of Uganda. We will stratify participating schools by geographical setting (rural, semi-urban, or urban) and ownership (public or private).

The Informed Healthcare Choices (IHC) primary school resources consist of a textbook and a teachers’ guide. Each of the students in the intervention arm will receive a textbook and attend nine lessons delivered by their teachers during a school term, with each lesson lasting 80 min. The lessons cover 12 key concepts that are relevant to assessing claims about treatments and making informed health care choices. The second arm will carry on with the current primary school curriculum.

We have designed the Claim Evaluation Tools to measure people’s ability to apply key concepts related to assessing claims about the effects of treatments and making informed health care choices. The Claim Evaluation Tools use multiple choice questions addressing each of the 12 concepts covered by the IHC school resources. Using the Claim Evaluation Tools we will measure two primary outcomes: (1) the proportion of children who ‘pass’, based on an absolute standard and (2) their average scores.

**Discussion:**

As far as we are aware this is the first randomised trial to assess whether key concepts needed to judge claims about the effects of treatment can be taught to primary school children. Whatever the results, they will be relevant to learning how to promote critical thinking about treatment claims.

Trial status: the recruitment of study participants was ongoing at the time of manuscript submission.

**Trial registration:**

Pan African Clinical Trial Registry, trial identifier: PACTR201606001679337. Registered on 13 June 2016.

**Electronic supplementary material:**

The online version of this article (doi:10.1186/s13063-017-1958-8) contains supplementary material, which is available to authorized users.

## Background

Health literacy, as defined by Healthy People 2010, is ‘the degree to which individuals have the capacity to obtain, process and understand basic health information needed to make appropriate health care decisions’ [1]. There has been an explosion in communication avenues for all types of information, including health, and children as well as adults are bombarded with all sorts of claims about the benefits and harms of treatments. This includes claims about conventional medicines, herbal medicines and nutritional therapies, dietary supplements, cleansing therapies, massage, reflexology and many other types of treatments. Belief in false claims about treatments causes harm and wastes resources. Not believing reliable claims means that effective treatments are not used. These problems are especially serious in resource-poor settings, where people have few resources to waste and a large burden of disease.

Several studies have concluded that people’s ability to assess health information is generally low and, in most cases, lacking [2–9]. While some studies have assessed adult health literacy and parental health literacy, only a few have focussed on health literacy among children and all these studies have been done in high-income countries [10–13]. Health-related knowledge, attitudes and behaviours developed during childhood are increasingly being recognised as foundational, deeply rooted and resistant to change later, when children become adults [14, 15], yet we have not been able to identify any studies that have addressed children’s assessment of claims about treatment effects. Children between the ages of 10 and 12 years in some countries are taught about fair tests and critical appraisal [16], but not with a focus on health or specifically teaching them to assess claims about the effects of health care interventions (which we will refer to as treatments).

An overview of six systematic reviews of educational interventions in low- and middle-income countries found 227 studies in total that reported student learning results [17]. None of these studies addressed health or scientific literacy or critical thinking more broadly. A systematic review of the effects of instruction on the development and enhancement of critical thinking skills at any age, and in any setting, found 49 studies of the effects of strategies for teaching primary school children (aged 6 to 10 years) to think critically [18], none of which focussed specifically on health literacy or assessing claims about treatment effects. Similarly, reviews that have focussed specifically on teaching children critical appraisal skills in relation to health have not found any studies that evaluate the effects of strategies to teach these skills to primary school children anywhere [19–21].

Teaching children how to assess claims about the effects of treatments might be effective for several reasons. First, children are capable of learning about fair tests and critical appraisal between the ages of 10 and 12 years and teaching these basic skills is already part of the curricula in some countries [16].

Second, it is possible to reach a large segment of the population before they drop out of school, since large numbers of children drop out after primary level in low-income countries [22–24]. The UN Educational, Scientific and Cultural Organisation (UNESCO) has estimated that 68% of children in Uganda who enrol in primary school are likely to drop out before finishing the prescribed 7 years [25]. Primary school in Uganda comprises seven classes from primary one (grade 1) to primary seven (grade 7) completed during a period of 7 years, with the official age range for primary education level being 6–12 years [26]. However, children attending primary school are generally aged between 6 and 17 years or even older in some schools, especially in conflict-torn areas [24].

Third, teaching children at primary school level to assess claims about treatments can capitalise on children’s natural curiosity and enthusiasm to learn.

Fourth, there are opportunities for children to share what they have learned with other children and family members (parents or guardians). In addition, primary schools play an important role in many communities in sub-Saharan Africa, particularly Uganda, where 49% of the population are below the age of 15 years [27]. Teaching basic concepts in schools about how to assess claims about the effects of treatments might create opportunities for both the children and their families to learn the critical appraisal skills that they need when assessing the benefits and harms of treatments. Finally, a good foundation for a healthier society might result from teaching children to ask questions about treatment claims and how to assess health information about treatment effects before the formation of problematic health attitudes and behaviours in adulthood [14, 15].

For these reasons, we have developed and pilot-tested resources to help teach children how to assess claims about the benefits and harms of treatments. We will evaluate the effects of these resources on knowledge in a randomised comparison with the standard curriculum.

In parallel, we have developed a podcast to teach some of the same concepts to parents of these children. We will test the effects of the podcast in a linked individual-randomised trial [28]. In that trial, we will randomly allocate 500 parents of some of the children in this trial to either listen to the podcast or to typical public service announcements about health issues. The parents will be volunteers, recruited from both intervention and control schools. We will use the same outcome measure in both trials, and we will measure the effects of the podcast on the children of parents included in that trial, and the effects of the primary school resources on those parents.

## Objectives

This research will address the following question: Does use of the Informed Healthcare Choices (IHC) school resources improve children’s ability to assess claims about treatment effects?

The primary objective of this study is to measure the impact of the IHC school resources on children’s ability to assess claims about treatment effects.

Secondary objectives of the study are to measure effects on the proportion of children who achieve a score indicating mastery of the 12 concepts covered by the primary school resources, their understanding of and ability to apply specific concepts relevant to the assessment of claims about treatment effects, intended behaviours, self-efficacy, attitudes towards school, attendance and academic achievement.

## Methods

This will be a two-arm, cluster-randomised trial as illustrated in the flow chart below (Fig. 1). Because the intervention will be delivered by teachers in primary schools, we will randomise schools rather than individual children. However, the objective – improving children’s ability to assess claims about treatment effects – pertains to individual children.

**Fig. 1 Fig1:**
[figure not shown]
Study flow chart

## Study population and random allocation

The study population will consist of primary-five (grade-5) children enrolled in school at the time of the study. Primary-five children in Uganda are, on average, between 10 and 12 years old, but in some cases older, especially in conflict prone areas. Within each participating school, we will include all primary-five children.

We will ask the head teachers of the participating schools to select the primary-five teachers who will deliver the lessons using the IHC primary school resources (or who would have done so in the control schools). There will be no inclusion or exclusion criteria for the teachers, other than that they provide written consent to participate in the trial. The recruitment process will be done starting 1 April 2016 to 31 July 2016.

### Inclusion and exclusion criteria

#### Inclusion

Public and private primary schools in the central region of Uganda will be eligible to participate. Primary-five students in those schools will be included in the study.

#### Exclusion

We will exclude international schools, special needs children’s schools for the deaf and blind, and schools that participated in the user testing and piloting of the resources. Children in primary level classes other than primary five will be excluded from participating in the study. For practical reasons, we will exclude schools that are too difficult to access.

Only schools which agree to participate and sign a Consent Form for participation will be included in the trial.

### Sampling technique

We will use a multistage sampling technique in which we will first draw a sample of districts from all the districts in the central region in Uganda. In the second stage we will randomly sample schools proportionately from the selected districts, stratifying by school setting (urban, semiurban and rural areas), and further by ownership (privately funded and government-aided schools). According to the Uganda Bureau of Statistics, urban areas in Uganda are defined as gazetted cities; municipalities and town councils with a population of over 2000 persons; rural areas comprise villages in remote or isolated areas, usually with a population of less than 2000 people; and semi-urban areas are those found on the periphery of gazetted cities and municipalities with a population of close to 2000 people [26]. We will select a minimum of 110 schools at random using on-line software (www.sealedenvelope.com).

### Random allocation

Schools will form the basic units (clusters) for allocation. Each school will be numbered and listed, and the study arm allocation will be determined using computer-generated randomisation, with equal numbers of the schools allocated to each arm in each stratum.

A statistician who is not a member of the research team will use computer-generated allocation sequences (www.sealedenvelope.com) to randomly allocate schools to either the control or intervention arm. No changes to allocation will be made subsequent to this.

We will use a block size of 4, with equal allocation ratios in each block and strata. The lists for each district will be randomly generated as shown in the table below (Table 1).

**Table 1 Tab1:** Examples of random allocation sequence

Block identifier	Block size	Sequence within block	Treatment	Location	Ownership	Code
1	4	1	Group A	Rural	Government	FZ4
1	4	2	Group A	Rural	Government	MG9
1	4	3	Group B	Rural	Government	NC5
1	4	4	Group B	Rural	Government	ID9
2	4	1	Group B	Rural	Government	VO9
2	4	2	Group B	Rural	Government	UA4
2	4	3	Group A	Rural	Government	KB5
2	4	4	Group A	Rural	Government	OQ6

As shown above (Table 1), the statistician will prepare a randomisation list with unique codes and corresponding allocation groups for each participating school. We will prepare separate lists for each stratum; i.e. rural-government for a rural school owned by government, rural-private for a rural school owned privately; suburban-private for a suburban school that is owned privately, suburban-government for a suburban school that is owned by government, urban-private for an urban school owned privately, and urban-government for an urban school that is government owned. These will contain only the participant school’s study code. Study allocation groups (intervention or control) corresponding to each study code will be inserted in envelopes and sealed. Every envelope will contain its study code as a label. For example, if the school is located in a rural area and it is a government school, a list will be prepared from the general list for that particular district. Below is an example of the study groups with corresponding study codes (Table 2).

**Table 2 Tab2:** Example of study groups and corresponding study codes

Treatment	Code
Group A	FZ4
Group A	MG9
Group B	NC5

## The intervention

The IHC primary school resources include a textbook and a teachers’ guide [29, 30]. We developed the resources iteratively between 2013 and 2015, using brainstorming, pilot testing and user testing. We began by identifying 32 concepts that people need to understand and apply to be able to assess treatment claims and make informed health care choices [31] and prioritising concepts that are relevant to primary school children [32]. There are six groups of concepts (Table 3).

**Table 3 Tab3:** Six groups of concepts that people need to understand and apply to be able to assess treatment claims and make informed health care choices [31]

1. Recognising the need for fair comparisons of treatments	
2. Judging whether a comparison of treatments is a fair comparison	
3. Understanding the role of chance	
4. Considering all the relevant fair comparisons	
5. Understanding the results of fair comparisons of treatments	
6. Judging whether fair comparisons of treatments are relevant	

Based on the findings of pilot testing, we reduced the number of concepts addressed in the resources to 12 concepts (Table 4), with the intention of developing additional resources in the future to introduce new concepts and reinforce understanding of those concepts. This approach is consistent with the principles of a ‘vertically aligned’ or spiral curriculum [33] which specifies where learners should begin and how they should progress. It avoids the trap of trying to teach or learn everything about a topic on the first cycle and helps to prevent learners being unprepared at later stages.

**Table 4 Tab4:** Twelve key concepts that are taught in the Informed Healthcare Choices (IHC) primary school resources^a^

1. Recognising the need for fair comparisons of treatments
1.1 Treatments may be harmful
1.2 Personal experiences or anecdotes (stories) are an unreliable basis for assessing the effects of most treatments
1.4 Widely used treatments or treatments that have been used for a long time are not necessarily beneficial or safe
1.5 New, brand-named, or more expensive treatments may not be better than available alternatives
1.6 Opinions of experts or authorities do not alone provide a reliable basis for deciding on the benefits and harms of treatments
1.7 Conflicting interests may result in misleading claims about the effects of treatments
2. Judging whether a comparison of treatments is a fair comparison
2.1 Evaluating the effects of treatments requires appropriate comparisons
2.2 Apart from the treatments being compared, the comparison groups need to be similar (i.e. ‘like needs to be compared with like’)
2.5 If possible, people should not know which of the treatments being compared they are receiving
3. Understanding the role of chance
3.1 Small studies in which few outcome events occur are usually not informative and the results may be misleading
4. Considering all the relevant fair comparisons
4.1 The results of single comparisons of treatments can be misleading
5. Understanding the results of fair comparisons of treatments
5.1 Treatments usually have beneficial and harmful effects

^a^The numbers indicate the grouping of the concepts (Box 1) and the numbering of the concepts in each group [31]

We designed the resources to be taught over a period of 9 weeks, with one double lesson per week during a single term and 1 h for completing the Claim Evaluation Tools. There are three school terms per year in Ugandan primary schools, with school terms ranging between 12 and 14 weeks per term, and lessons are taught in 40-min periods [24]. In addition to reducing the number of concepts introduced initially, we increased the time for each lesson from one to two periods (double lessons) to address the major barrier we found in the pilot testing, which was insufficient time (see Fig. 2, which equates to the SPIRIT figure for this trial).

**Fig. 2 Fig2:**
[figure not shown]
Enrolment schedule

### The textbook, exercise books and reminders

The textbook consists of a story told in a comic book format (Fig. 3), classroom activities, exercises, a checklist summarising the main lessons, and a glossary. In addition to the textbooks, we will provide each school with an exercise book for each pupil, a poster of the checklist for the classroom, and the lyrics and music to a song that includes reminders of key concepts.

**Fig. 3 Fig3:**
[figure not shown]
An excerpt of the comic book story

The contents of the book are as shown in Table 5.

**Table 5 Tab5:** Contents of the textbook

Introduction	
Chapter 1 Health, treatments and effects of treatments	
John and Julie learn about *claims* about treatments	
Chapter 2 Someone’s experience using a treatment	
Chapter 3 Other bad bases for claims about treatments (Part 1)	
Chapter 4 Other bad bases for claims about treatments (Part 2)	
John and Julie learn about *comparisons* of treatments	
Chapter 5: Comparisons of treatments	
Chapter 6: Fair comparisons of treatments	
Chapter 7: Big enough fair comparisons of treatments	
John and Julie learn about *choices* about treatments	
Chapter 8: Advantages and disadvantages of a treatment	
Review	
Chapter 9: Review of what is most important to remember from this book	

### The teachers’ guide

The teachers’ guide includes the following for each chapter, in addition to the chapter from the textbook:The objective of the lessonA lesson preparation planA lesson planA list of materials that the teacher and children will needA synopsis of the storyKeywords in the chapterReview questions to ask the children after reading the storyExtra examples for illustrating the conceptsBackground about the claims used in the story to illustrate the conceptsInstructions for the classroom activityAnswers and explanations for the activityAnswers and explanations for the exercisesBackground for the teacher, explaining the concepts using language and examples that are appropriate for teachers and keyword definitions for teachers

### Delivery of the intervention

We will contact participating schools 2 to 3 months before the start of the trial and invite all participating teachers in the intervention group to attend a 2-day introductory meeting. At the meeting we will inform them about the study objectives and procedures, including the Claim Evaluation Tools that we will use as an outcome measure, introduce them to the IHC primary school resources, and address any queries or concerns that may arise. We will discuss the general nature of the evaluation tool, but will not give the teachers copies of the questionnaire. We will try to contact or visit all the teachers in the intervention group who are unable to attend a meeting.

At least 1 week before the trial commences (and prior to the introductory meeting) we will give teachers in the intervention group the teachers’ guide to enable them to familiarise themselves with the content and prepare a semester plan for delivering the lessons. We will deliver the textbooks to the schools in the intervention group at least 1 week before the trial starts. We will use class lists provided by the school heads to ensure that each school receives an adequate number of books for all the primary-five children in the school.

To help ensure that the intervention is delivered as planned, we will monitor delivery of the intervention. We will do this by following guidelines of the Ministry of Education school supervisory timetable. These allow for follow-up of newly introduced programmes within schools [34]. We will encourage the teachers to make summaries after reading each chapter in the teachers’ guide in preparation for the lesson and we will ask them to hand these in to the study team after the intervention period. This will help to ensure that the teachers read the teachers’ guide in preparation for the lessons.

We will contact the schools allocated to the control group at the beginning of the school term to inform them about the study and study procedures and the evaluation tool that we will use as an outcome measure. We will tell them that they will receive the IHC primary school resources at the end of the study, but we will not introduce them to the resources or invite them to the introductory meeting.

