## Blinding

The comparison will not be blinded. All of the participants in the trial will be informed of the purpose of the study and will know whether they are in the intervention or control arm. The head teachers and the district education officers will be informed of the purpose of the study when they are recruited. The primary-five teachers in both arms of the trial will be informed of the purpose of the study prior to the delivery of the intervention. Children in both arms of the trial will be informed of the purpose of the Claim Evaluation Tools when they are asked to complete them. They will also be asked to put their names on the questionnaires and will be told that they and their teachers will be told their scores.

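### Teachers in the intervention arm get a fuller briefing on the outcome test than control schools, which leaves a small, avoidable risk of test preparation in one arm

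*Protocol article*

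**What the plan says.** All statements on how teachers learn of the outcome test stand in the protocol article, mainly in Delivery of the intervention.

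- **Intervention arm.** The investigators will "invite all participating teachers in the intervention group to attend a 2-day introductory meeting". The agenda covers the study's objectives and procedures, "including the Claim Evaluation Tools that we will use as an outcome measure", then an introduction to the resources, then queries and concerns. On depth, the article says: "We will discuss the general nature of the evaluation tool, but will not give the teachers copies of the questionnaire". Teachers who cannot attend are to be contacted or visited where possible.
- **Control arm.** Contact is made when term begins, and its content is given only as "inform them about the study and study procedures and the evaluation tool that we will use as an outcome measure". Control schools are promised the resources after the study, but "we will not introduce them to the resources or invite them to the introductory meeting".
- **Both arms.** The Blinding section states that the comparison is not blinded and that teachers in both arms learn the study's purpose before delivery starts. On test scores it says, of the children in both arms: "They will also be asked to put their names on the questionnaires and will be told that they and their teachers will be told their".

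The Abstract and the section The intervention define what is being tested as a textbook and a teachers' guide. Outcome assessment states that the test has 24 multiple-choice items on the 12 concepts that the resources teach, taken by both arms in class at the end of term.

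**The concern.** The Objectives ask whether using the resources improves children's ability to assess treatment claims. For the comparison to answer that, the arms should differ in the resources and their delivery, and not in what teachers know about the trial's own measuring instrument. As described, intervention teachers can discuss the test and ask about it over two days, whereas control schools are informed of it.

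A teacher who knows more about the form of a test can, deliberately or not, lean lessons towards it. Any gain from that would raise scores on this instrument without a matching gain in the underlying ability. It would also not arise where the resources are later used outside the trial, since no such test would be set there. Both primary outcomes, the pass proportion and the mean score, come from the same 24 items, so such a gain would push both in the intervention's favour.

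**Working it through.** The article has no figure for this point, so the check sets the statements side by side.

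1. **Is the tool disclosed in both arms?** Yes. Both are told of the same tool. This limits the concern to a difference in depth and setting.

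2. **Is the depth stated to be the same?** No. For the intervention arm the text describes a discussion of the tool's general nature, in a meeting that takes queries. For the control arm it says only that schools are informed, and it rules out the introductory meeting. This difference is in the stated procedures. It is not inferred from something the article leaves out.

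3. **Is the timing different?** This is not established. Control schools are contacted at the beginning of term. The date of the meeting is not given. The Blinding section puts information on the study's purpose before delivery in both arms.

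4. **Does the briefing belong to the intervention?** The article's own arrangement says no. Delivery of the intervention lists the tool with study objectives and procedures, and lists the introduction to the resources as a separate item. Introducing the resources is part of delivery. Explaining the trial's test is a trial procedure.

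5. **Could teachers act on it?** The setting allows it. The trial is unblinded and teachers will be told scores. Children are told the purpose of the tool only when asked to complete it, so teachers are the obvious route for any earlier preparation. Intervention teachers are also the ones teaching the 12 tested concepts, so they can more readily use a fuller briefing. The match between test and taught content is legitimate in itself.

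6. **What limits the risk?** Copies of the questionnaire are withheld, which guards against leakage of items. It does not equalise what teachers are told about the form of the test.

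7. **Can a size be computed?** No. The Sample size section gives an expected control pass proportion of 0%, a difference of 10% to detect, and a remark on one more correct answer. None of these describes an effect of preparation. Turning an assumed gain in items into a change in pass proportion would also need a control score distribution, which the article does not give.

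**The case against.** The strongest reply is that the article already handles this reasonably. The sentence about the tool's general nature is a safeguard, since it says that the questionnaire is not handed out. Both arms know of the same tool before an end-of-term test. Some information is unavoidable, because an hour has to be set aside for the test and participants are to be fully informed of the study's purpose. How control schools are briefed in detail is something that a condensed article may leave to the full protocol. A scripted sheet would itself disclose the format.

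Most of this stands, and it is why the point is minor. What remains is that the article describes two different procedures where one would do. A sheet does disclose the format, but equally, and equal disclosure does not bias the contrast.

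A reader might infer more than the documents support:

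- **That pupils rehearse the instrument.** No passage describes practice items or practice sessions.
- **That intervention teachers learn of the test before planning their lessons.** The teachers' guide, supplied so that they can prepare a semester plan, reaches them before the meeting. Planning may therefore start before the test is discussed.
- **That score feedback gives intervention teachers a special motive.** The Blinding section describes feedback for children in both arms, so it does not separate the arms. It is only part of the setting in which unequal knowledge could matter.
- **That the bias is large relative to the planned difference.** Any such figure would rest on an assumed preparation effect.

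**Conclusion.** The point holds as a minor, partly mitigated risk of performance bias. The arms are briefed differently on the outcome instrument, the briefing is not part of the resources under test, and in an unblinded trial with scores returned to teachers the difference can only be expected to favour the intervention, if it acts at all. No error or contradiction is shown, and no preparation is documented. The size is unknown and cannot be derived from the document.

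The conclusion rests on two readings of the article. One is that being informed means less than a discussion with queries. The other is that listing the tool under study procedures places it outside the intervention. If the full protocol already prescribes the same description of the tool for both arms, the concern falls away.

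**What to change.** Replace the discussion of the Claim Evaluation Tools at the introductory meeting with one scripted written description, for example that children will sit a one-hour multiple-choice test in class at the end of term. Give it to teachers in both arms with identical wording and at the same time, with the same request not to practise for the test. Continue to withhold the questionnaire. The rest of the meeting, which introduces the resources, can stay as it is.

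The cost is a change to the agenda and one information sheet. The small downside is that teachers' questions about the test have to be referred to the sheet. If the meetings have already been held, name the difference in briefing as a limitation when the results are reported.
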